#### Exclusion criteria

Patient is potentially eligible for curative treatment.Patient has a tumour biomarker that clearly indicates the presence and type of cancer (e.g. highly elevated prostate-specific antigen [PSA]).Clinical suspicion of lymphoma > 20%.
Some features may be suggestive of lymphoma, including fever or night sweats (i.e. B symptoms excluding weight loss), or imaging showing well-defined, homogenous lymphadenopathy. These findings are not exclusion criteria specifically, but should be considered by the clinician in formulating their differential diagnosis.

### Pre-treatment evaluation

History and focused physical examination (as needed).Eastern Cooperative Oncology Group (ECOG) performance status.Cross-sectional imaging (e.g. CT, MRI, PET/CT) within 3 months.Physician pre-treatment baseline questionnaire.
Treating physician must consider the pre-test probability of cancer as > 95% based on clinical judgement/radiological findings, and deem the probability of lymphoma < 20%.Patient must not be considered potentially eligible for curative treatment.
Radiation plan documented (dose/fractionation, site).ESAS quality of life score.

### Evaluation during treatment

No additional evaluations are required during treatment, apart from regularly scheduled visits with the treating physician. The treating physician should ask about any adverse events and biopsy complications during patient appointments, and document them in the patient’s chart as per institutional practice.

### Follow-up

In keeping with a pragmatic trial design [6], we will limit the number of additional follow-up visits beyond routine practice. We will do one follow-up either in person or over the telephone 4 weeks after RT or 2 weeks after biopsy, whichever is later. The purpose of this follow-up will be to assess for symptomatic response to radiation and monitor for adverse events from the biopsy. We will also obtain an ESAS score at the follow-up visit.

Post-treatment management questionnaires should be completed by the treating radiation oncologist (within 3 months of enrolment), which includes:

Biopsy result, including histological and molecular diagnosis.Biopsy complications.Preferred management plan if biopsy results were known prior to enrolment/radiation.

In addition, we will review the participant’s chart 1 year after enrolment, to determine the survivorship status of the patient.

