### Study endpoints

#### Primary endpoint

Rate of “inappropriate use of radiation”, defined as the percentage of patients in whom management would have differed if the biopsy results were known prior to radiation. These cases meet the definition either when:
Biopsy pathology clearly shows a non-malignant entity.Or the biopsy shows malignancy, but the patient would have received upfront systemic therapy or an alternate therapy, rather than radiotherapy, had the biopsy results been known.

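### The management judgement that decides the second arm of the primary endpoint is normally recorded once the response to radiation is known, so hindsight can misclassify cases in either direction.

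*Protocol article*

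**What the plan says.** Under Primary endpoint, the rate of inappropriate radiation is "defined as the percentage of patients in whom management would have differed if the biopsy results were known prior to radiation". There are two routes to an event:

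- **Limb 1:** "Biopsy pathology clearly shows a non-malignant entity". Pathology decides this.
- **Limb 2:** pathology confirms a cancer, yet "the patient would have received upfront systemic therapy or an alternate therapy, rather than radiotherapy, had the biopsy results been known". This needs a judgement about what would have been done.

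The Follow-up section states who makes that judgement and when: "Post-treatment management questionnaires should be completed by the treating radiation oncologist (within 3 months of enrolment"). One of the listed items is "Preferred management plan if biopsy results were known prior to enrolment/radiation". The single mandated visit falls at "4 weeks after RT or 2 weeks after biopsy, whichever is later", and the same section says "The purpose of this follow-up will be to assess for symptomatic response to radiation". The Adverse events section places the post-treatment questionnaire at this visit. It also has the questionnaire cover wound healing beyond 6 weeks after biopsy.

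Pre-treatment evaluation lists a "Physician pre-treatment baseline questionnaire". The contents shown are the probability of cancer, the probability of lymphoma and ineligibility for curative treatment.

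**The concern.** The endpoint asks whether radiation was the right first choice given the biopsy result. How the patient responded to radiation is not part of that question, yet the person answering normally knows it, and nothing in the article asks for it to be set aside. A physician who has seen relief may find it easier to say that radiation would have been chosen anyway. One who has seen no benefit may find it easier to say the opposite.

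At stake are the trial's only formally tested endpoint and the interim safety rule, which counts the same events. The numbers involved are small, so a few misclassified patients matter.

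**Working it through.** **1. The plan's own figure.** Statistics and sample size calculations gives a one-sided one-sample binomial test, null rate 20%, expected rate 5%, 5% significance, 90% power, 10% drop-out and 48 patients. In the exact binomial calculation, the smallest n from which these targets are met is 44, with success at 4 or fewer events:

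- P(X ≤ 4 | n = 44, p = 0.20) = 0.044
- P(X ≤ 4 | n = 44, p = 0.05) = 0.933
- 44 / 0.9 = 48.9, and 44 × 1.1 = 48.4

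The stated 48 is therefore reproduced to within a patient.

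**2. Sensitivity at the boundary.** With 44 evaluable patients:

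| Events | One-sided p against 20% | Result |
|---|---|---|
| 4 | 0.044 | pass |
| 5 | 0.102 | fail |

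The limit stays at 4 events for any evaluable number from 44 to 48. At that limit, one case moved from event to non-event turns a fail into a pass, and one moved the other way does the reverse.

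**3. When the judgement is made.** The questionnaire belongs to a visit at least 4 weeks after radiation, at which response is assessed. It includes an item that can only be answered more than 6 weeks after biopsy. The 3-month limit is a latest date and no earliest date is given, so some forms could precede the response, but that is not the normal sequence described.

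**4. Illustration of size.** The documents give no misclassification rate, so these inputs are assumptions: a true rate of 20%, a share s of true events that come from limb 2, and a fraction m of those recorded as non-events. Only downward error is modelled here. The recorded rate is 0.20 × (1 − s × m). The false-pass probability is P(X ≤ 4 | 44, recorded rate). The interim stop, from Planned safety interim analysis, is P(X ≥ 5 | 24, recorded rate).

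| s | m | Recorded rate | False pass | Interim stop |
|---|---|---|---|---|
| – | 0 | 0.2000 | 4.4% | 54% |
| 0.50 | 0.10 | 0.1900 | 6.1% | 49% |
| 0.75 | 0.10 | 0.1850 | 7.1% | 46% |
| 0.50 | 0.25 | 0.1750 | 9.6% | 41% |
| 0.75 | 0.25 | 0.1625 | 13.7% | 35% |

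Error in the other direction would raise the recorded rate. That would make a pass less likely and an interim stop more likely.

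**5. Whether an earlier judgement is possible.** Timing of biopsy and radiation requires the result to be unavailable when radiation starts, so the result cannot be applied before then. The rule for reading it can be recorded before then. The Background and Risks to subjects sections already name the kinds of malignancy in mind: lymphoma, small cell lung cancer and germ cell tumour.

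**The case against.** The strongest reply is that the item asks exactly what the endpoint definition requires, and that a patient-specific answer to an actual result has to come after radiation has at least begun. There is no contradiction in the text. The named examples already tie the obvious limb-2 cases to histology, and the biopsy result sits on the same form, so an implausible answer would be visible. The article may also condense a fuller baseline form. A pre-recorded list would be written by the physician who has just chosen urgent radiation and may carry its own commitment bias.

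Much of this stands. The point concerns a design choice and is not an error in the text. The full baseline form is not shown, and the examples leave less room for hindsight in clear cases. What does not stand is the argument that a late judgement is unavoidable, because the decision rule can be fixed beforehand. A pre-recorded rule may reflect the physician's prior preference, but it cannot be influenced by the response.

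A reader might go further and infer that the error runs mainly towards non-events, so that the trial's type I error is inflated. The documents do not support that. Knowledge of outcome can push either way. The argument for a downward tilt rests on who makes the judgement (the physician who chose radiation), and its timing alone gives no direction. A reader might also infer that one reclassified case decides the trial. That is so only when the count lies at the limit, as with any exact binomial rule.

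**Conclusion.** The point holds in a limited form. For limb 2, the classification is normally made with the outcome of radiation known, and this can misclassify cases in either direction. Limb 1 is not affected.

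The size and net direction cannot be derived from the documents. The rise in false-pass probability from 4.4% to 6–14%, and the fall in interim stopping from 54% to between 49% and 35%, show only what would follow from the assumed inputs: a true rate of exactly 20%, 50–75% of events from limb 2, 10–25% of those missed, no error upwards and 44 evaluable patients. They do not estimate the bias in this trial. The trial remains interpretable as planned, and the change below is a worthwhile, inexpensive improvement.

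**What to change.** Unless the full baseline form already does this, add one item to the physician baseline questionnaire, completed before the first fraction: which categories of biopsy result would lead this physician, for this patient, to a plan other than upfront radiation. The protocol's own three examples can be listed, with space for others the physician names.

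State under Primary endpoint or Follow-up that limb 2 is classified by applying that answer to the pathology result. Keep the post-treatment answer for results not foreseen at baseline, and repeat the primary analysis with the post-treatment answer throughout as a sensitivity analysis.

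The cost is one more baseline item in an urgent setting and a sentence in the protocol. No visits, patients or treatment change. Unforeseen results would still depend on the later judgement.

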### Intervention

#### Radiation treatment

Radiation technique, volumes and dose/fractionation schemes will be decided by the treating radiation oncologist based on consideration of disease site, volume of tumour, nearby organs at risk, likely histology, performance status, patient age and prognosis. This allows a high flexibility of delivery, intended to keep the trial pragmatic and in keeping with real world practice [6]. It is not recommended to spare part of the tumor solely to allow for a biopsy.

#### Biopsy

Biopsies should be taken at whichever site is clinically preferred, typically the most anatomically feasible site of biopsy (regardless of whether it has been irradiated), considering institutional wait times and availability for different biopsy procedures. If the first biopsy attempt is unsuccessful, the second attempt can be a repeat biopsy at the same site or at another site.

#### Timing of biopsy and radiation

If the patient’s biopsy has not yet been ordered at the time of enrolment, it should be ordered immediately. The biopsy should be done at the earliest possible time, and if it is performed before radiation, or during radiation, the biopsy should proceed and the radiation should continue as planned. A biopsy may be completed before the patient is enrolled on trial as long as the biopsy result is not yet available at the time of enrolment (and at the start of radiation treatment).

### Adverse events

We will not be routinely evaluating for adverse events from radiation since these patients are receiving radiation regardless of enrolment (the trial is simply studying the *timing* of radiation in relation to biopsy).

However, we will actively evaluate for biopsy complications as it is possible that the frequency or severity of biopsy complications could increase if done within an irradiated area. In the follow-up visit post-treatment questionnaire, we will specifically evaluate for the following complications:

Pneumothorax (requiring a chest tube).Wound infections (requiring antibiotics).Prolonged bleeding from biopsy site.Fistula formation.Delayed wound healing, defined as non-healing wound or dehiscence at biopsy site > 6 weeks following the biopsy (requiring a specialist wound care team or continued antibiotics) – this should be assessed from the chart and included in post-treatment questionnaire.

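### Delayed wound healing can be declared only more than 6 weeks after biopsy, but the form that records it is not timed from the biopsy, so this one item can be missed

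*Protocol article*

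**What the plan says.** The Adverse events section promises active evaluation of biopsy complications and names the instrument: "In the follow-up visit post-treatment questionnaire, we will specifically evaluate for the following complications". Five complications follow. Only the last carries a minimum time: "Delayed wound healing, defined as non-healing wound or dehiscence at biopsy site > 6 weeks following the biopsy". The same sentence restricts it to cases needing specialist wound care or ongoing antibiotics, and adds that "this should be assessed from the chart and included in post-treatment questionnaire".

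The Follow-up section sets the timing. There is one mandated contact, at "4 weeks after RT or 2 weeks after biopsy, whichever is later". It then says: "Post-treatment management questionnaires should be completed by the treating radiation oncologist (within 3 months of enrolment"). Biopsy complications are among the contents of that form. The only later look is a review of the "chart 1 year after enrolment, to determine the survivorship status of the patient".

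On biopsy timing, the section on timing of biopsy and radiation says "The biopsy should be done at the earliest possible time" and gives no maximum interval from enrolment. It also allows a biopsy before enrolment if the result is still pending. The Biopsy section allows a second attempt and does not move the questionnaire deadline.

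**The concern.** The definition counts from the biopsy, the deadline counts from enrolment, and the visit may count from either radiation or biopsy. An item that needs more than 6 weeks of observation after biopsy can therefore be due for recording before that time has passed. A form completed too early would show no delayed healing simply because the condition could not yet be declared.

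At stake is the biopsy complication rate, a secondary endpoint that the Study design section sets against an institutional average of 5–10%. The Background treats added biopsy complications as one of four issues clinicians want to avoid. It also notes that an earlier review of biopsies in irradiated tissue may have underestimated low-grade events because its studies relied on charts or patient reports. For this item the trial itself turns to the chart without saying when to look. Missed cases can only lower the observed rate.

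**Working it through.** The plan gives no figure to reproduce here; the check is a timeline in weeks from enrolment.

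**Inputs**
- Definition: more than 6 weeks (42 days) after biopsy (Adverse events).
- Visit: the later of radiation + 4 weeks and biopsy + 2 weeks (Follow-up).
- Questionnaire deadline: 3 months from enrolment, taken as 13 weeks or 91 days (Follow-up).
- Biopsy week *b*: not bounded above in the article.
- End of radiation *R*: not fixed. The visit's 4 weeks are assumed to count from the end of radiation. Counting from its start would bring the visit no later.

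**Step 1: can the visit see the event?**

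Visit − biopsy = max(*R* + 4 − *b*, 2).

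- This exceeds 6 only if *R* − *b* > 2, so the biopsy must precede the end of radiation by more than 2 weeks.
- If the biopsy is at or after the end of radiation (*b* ≥ *R*), the gap is at most 4 weeks.
- If it is 2 weeks or more after radiation (*b* ≥ *R* + 2), the gap is exactly 2 weeks, at least 4 weeks short.

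So a visit held on schedule cannot show the event in any patient biopsied after radiation. A form completed at that visit cannot record it.

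**Step 2: can the form, completed at its deadline, see the event?**

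Time from biopsy to deadline = 13 − *b*, which must exceed 6, so *b* < 7 (in days, 91 − 42 = 49).

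| Biopsy at week | Weeks from biopsy to deadline | More than 6? |
|---|---|---|
| 0 | 13 | yes |
| 2 | 11 | yes |
| 4 | 9 | yes |
| 5 | 8 | yes |
| 6 | 7 | yes |
| 7 | 6 | no |
| 8 | 5 | no |

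The window works for every biopsy before week 7 if the form is left until late enough. It fails for a first or repeat biopsy from week 7.

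**Step 3: does the documented wait reach week 7?**

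The only figure is in the Background: biopsy waits sometimes delay radiation by over a month. Read as 4–5 weeks from enrolment, that leaves 9 to 8 weeks before the deadline, so a single wait of that length fits. A longer wait, or a second biopsy after a failed first, may not. The article gives no distribution of either.

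**Step 4: scale**
- The benchmark for all complications in 48 patients: 0.05 × 48 = 2.4 and 0.10 × 48 = 4.8 events.
- One missed patient: 1/48 = 2.1 percentage points. If the planned 10% drop-out occurs, 48 × 0.9 = 43.2, and 1/43 = 2.3 points.

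These figures show the weight of one missed case. They do not estimate how many would be missed.

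**The case against.** The strongest reply is that the protocol foresaw the problem. The sentence that sets the 6-week criterion sends this item to the chart, so the early visit is not its intended source. The 3-month window is long enough for any biopsy before week 7, biopsies are to be done as early as possible, and some precede enrolment. A case that needs specialist wound care or continued antibiotics should leave a trace in the chart. Nothing says that the form locks at 3 months or that later information is discarded, and such detail may be in the full protocol or case report forms, which are not shown. The single literature figure in the Background, 17 of 2160, would give 17/2160 × 48 = 0.4 complications of any kind, although the article warns that it may be too low for minor events.

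Most of this stands, and it limits the point. It does not remove it. The article names the form after the visit, sets no earliest date for it, and fixes a deadline that ignores a late or repeat biopsy. Followed as written, that timing can defeat the chart assessment.

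A reader might go further and infer:
- *That late complications in general are structurally under-counted.* Only one of the five listed items has a 6-week criterion. No timing conflict is shown for fistula or the others, and the loss for this item is conditional.
- *That the primary endpoint is compromised because it uses the same form.* Judging inappropriate radiation needs the biopsy result and the physician's preferred management, not 6 weeks of healing. A week-7 biopsy still leaves 13 − 7 = 6 weeks before the deadline, and no figure in the document shows that to be too short.
- *That the comparison with the institutional 5–10% is biased by a known amount.* The article does not say how that average was ascertained.

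**Conclusion.** The point holds in a narrow form. The recording window for delayed wound healing is not tied to the biopsy that starts its 6-week clock. The item can be missed when the form is completed at the visit. It cannot be scored by the stated deadline after a first or repeat biopsy at about week 7 or later.

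The direction of any error is downward, and it touches one component of a secondary endpoint. Its expected size cannot be derived, because the article gives neither the distribution of biopsy dates nor the actual completion dates of the form. The interim stopping rules do not use the complication rate, so they are not affected.

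The conclusion rests on 3 months being about 13 weeks, on the visit counting from the end of radiation, and on the stated windows being followed. If the full protocol already lets the item be updated after 3 months, the week-7 limit falls away and only the missing earliest date needs attention. This is an optional improvement, worth making because it is cheap.

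**What to change.** Change the timing of this one item:
1. Assess wound healing from the chart more than 6 weeks after the last biopsy, that is from day 43.
2. Let the item's deadline run from the last biopsy instead of from enrolment. The rest of the form can keep its 3-month limit.
3. Add the item to the 1-year chart review as a backstop. With a year taken as 52 weeks, this covers any biopsy before week 52 − 6 = 46.

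The cost is a few words in the Follow-up and Adverse events sections and one added entry in a review already planned. No extra visit is needed, so the pragmatic design is kept. The downside is that some forms close a few weeks later: a biopsy at week 8, for example, could be scored only after week 14 instead of by week 13. The interim analysis waits for complete data on 24 patients, so the plan should say that this item need not be closed for that analysis, whose rules do not use it.

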### Statistics and sample size calculations

We hypothesize that the primary endpoint, rate of “inappropriate radiation”, will be no more than 5%. We consider it unacceptable if the rate of “inappropriate radiation” is ≥ 20%. Using a one-sided, one-sample binomial test, with 90% power at the 5% significance level, to reject the null hypothesis of a change rate of ≥ 20%, with 10% drop-out, we estimate that 48 patients are needed.

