### Data analysis

Patients who decline a biopsy after RT will be excluded from analysis of both primary and secondary endpoints. Patients for whom biopsy is repeatedly non-diagnostic after undergoing RT will be masked from analysis of the primary endpoint, since inappropriate use of RT cannot be determined without a biopsy. However, analysis of secondary endpoints will be conducted, including determination of overall rates of diagnostic yields/accuracy, complications from biopsy, and number of biopsy attempts.

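### Under the exact binomial test, 48 enrolled is one patient short of the stated 90% power at 10% drop-out: 49 are needed, and 48 gives about 88% on average

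*Protocol article*

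**What the plan says.** The section Statistics and sample size calculations takes 5% as the highest expected rate of inappropriate radiation and treats 20% or more as unacceptable. The null hypothesis is the 20% rate. The method is given as: "Using a one-sided, one-sample binomial test, with 90% power at the 5% significance level". The result is: "with 10% drop-out, we estimate that 48 patients are needed". The section gives no evaluable number and no critical number of events. It does not say whether the binomial test is exact, and it does not define drop-out.

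The section Data analysis names two groups that leave the primary analysis. For the first: "Patients who decline a biopsy after RT will be excluded from analysis of both primary and secondary endpoints". For the second: "Patients for whom biopsy is repeatedly non-diagnostic after undergoing RT will be masked from analysis of the primary endpoint". The primary test therefore runs on those who remain evaluable, not on all 48.

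**The concern.** The paragraph fixes every input needed to check its own result, and the result does not quite follow. If 10% of 48 patients are lost, the evaluable number falls just below the point at which the exact test reaches 90% power. The success rule also changes at that point: 4 inappropriate cases would reject the 20% rate with 44 evaluable patients, but not with 43. Readers will take 90% as the chance that the trial succeeds if the approach performs as hoped, so the figure should hold under the plan's own drop-out assumption.

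**Working it through.** **Inputs** (all from Statistics and sample size calculations): null rate p0 = 0.20; expected rate p1 = 0.05; one-sided alpha 0.05; power 0.90; drop-out 10%; 48 enrolled.

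**Exact test.** With n evaluable patients and X inappropriate cases, reject the 20% rate if X ≤ c. Here c is the largest value with P(X ≤ c | n, 0.20) ≤ 0.05, and power is P(X ≤ c | n, 0.05).

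| Evaluable n | Cutoff c | Alpha at c | Alpha at c + 1 | Power |
|---|---|---|---|---|
| 37 | 3 | 0.0450 | 0.1120 | 88.8% |
| 40 | 3 | 0.0285 | 0.0759 | 86.2% |
| 41 | 3 | 0.0244 | 0.0664 | 85.3% |
| 42 | 3 | 0.0208 | 0.0580 | 84.3% |
| 43 | 3 | 0.0178 | 0.0506 | 83.3% |
| 44 | 4 | 0.0440 | 0.1018 | 93.3% |
| 48 | 4 | 0.0248 | 0.0621 | 90.9% |

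No evaluable number below 44 reaches 90%; the best is 88.8%, at 37. From 44 up to the 99 checked, power is always at least 90%. The smallest sufficient evaluable number is therefore 44.

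**Reproducing the stated 48.** Multiplying by 1.1 gives 44 × 1.1 = 48.4, which rounds to 48. This is a probable explanation, though the article does not give its route. If 10% of those enrolled are lost, the correct step is division: 44/0.9 = 48.9, so 49. Check: 49 × 0.9 = 44.1, which leaves 44.

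**Power that 48 delivers.** 48 × 0.9 = 43.2, so 43 evaluable and 83.3% power. Reaching 44 allows 48 − 44 = 4 losses, or 4/48 = 8.3%.

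**Averaging over chance.** If each patient is lost independently with probability 10%, the evaluable number is binomial, and power can be averaged over it:

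- 48 enrolled: average power 88.4%; chance of 44 or more evaluable 47%.
- 49 enrolled: average power 89.5%; chance of 44 or more evaluable 63%.

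**Other readings of the test.** The uncorrected normal approximation gives

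n = [(1.645 × √(0.20 × 0.80) + 1.282 × √(0.05 × 0.95)) / 0.15]² = 39.04, so 40 evaluable, and 40/0.9 = 44.4, so 45 enrolled.

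With a continuity correction it gives 46 evaluable and 52 enrolled; the arcsine method gives 38 and 43. None of these gives 48.

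**Interim stop.** Stopping at 5 or more inappropriate cases among the first 24 does not change these powers. A trial stopped that way already exceeds the final cutoff of 3 or 4.

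**Further loss (assumption).** Suppose a further 5% of those remaining had repeatedly non-diagnostic biopsies. The evaluable share is 0.90 × 0.95 = 0.855, or about 41 of 48. Average power is then about 86%, and the chance of 44 or more evaluable is about 16%.

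**The case against.** The strongest reply is that the plan is essentially right. Its inputs reproduce 48 to within one patient. The 83.3% is the lowest power at any evaluable number from 37 to 48. It arises only because a cutoff of 4 at n = 43 gives alpha 0.0506 instead of 0.0500, and any small exact design shows such a step somewhere. On average, 49 enrolled would give 89.5% against 88.4% for 48, a gain of 1.1 points, and even 49 averages just under 90%. All of this stands, and it is why the point is minor. A reader might infer from the 83% that the trial is materially underpowered; the figures do not support that.

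A second reply is that the text does not call the test exact. Under the uncorrected normal approximation, 43 evaluable patients exceed the 40 needed, and 4 events among 43 would reject (z = −1.75). This also stands as a condition on the finding. It does not rescue the stated figure, because that method leads to 45 enrolled, while the exact test leads to 48 or 49.

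A reader might also infer that repeatedly non-diagnostic patients come on top of the 10%. The article does not show this. Drop-out is undefined and may already cover both groups removed in Data analysis. The background section puts non-diagnostic biopsy below 5%, and the Biopsy section allows a second attempt, so repeated failure should be rarer still. The 86% figure is therefore an illustration toward the pessimistic end.

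Finally, cutoffs for each evaluable number are detail that an article may leave to the full protocol or analysis plan, so their absence is not the finding. The finding is that the stated sample size, power and drop-out do not agree.

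**Conclusion.** Minor, but wrong as written. Under the exact one-sided 5% test of 20% against 5%, 90% power with 10% loss needs 49 enrolled, not 48. With 48, power is 88.4% on average and 83.3% at exactly 43 evaluable. The average shortfall is 1.6 points and the sample-size error is one patient. The conclusion rests on reading the binomial test as exact and on applying the 10% to those enrolled. The validity of the test is not in question: alpha stays below 5% at every evaluable number when the matching exact cutoff is used. Whether further losses lower power more cannot be settled from the article.

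**What to change.** Restate the sample-size paragraph as follows:

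- The test is the exact one-sided binomial test. It needs 44 evaluable patients and rejects the 20% rate if 4 or fewer have inappropriate radiation (alpha 0.044, power 93.3%).
- Enrolling 48 tolerates at most 4 non-evaluable patients.
- At 10% loss, power is about 88% on average. At exactly 43 evaluable, the cutoff is 3 or fewer and power is 83%.
- State whether the 10% covers patients who decline biopsy and those whose biopsies are repeatedly non-diagnostic. If it does not, give the allowance for them.

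This changes wording only, and no extra patients are needed. The cost is a slightly less favourable stated power. Enrolling 49 would correct the inflation step, at the cost of one patient.
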